## 5. Eligibility

### 5.1 Inclusion Criteria:

- Adult patients (> 18 years)
- CT or MRI proven acute ischemic (AIS) or hemorrhagic stroke (ICH) within 72h after onset of symptoms
- Severe hemiparesis (medical research council scale for muscle strength  $\leq 2$ )
- premorbid modified Rankin Scale (mRS)  $\leq 3$
- maximum National Institute of Health Stroke Scale Score (NIHSS) 25
- Voluntary written consent by the patient

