### **8.2. Secondary Outcome Measures:**

(i) Improvement of neglect measured with the Catherine Bergego Scale (CBS) part 5 and 6 on day 9 after admission to the hospital compared to baseline (Difference in scores on CBS scale between baseline before treatment and day 9 after treatment)

(ii) Improvement of arm motor function measured with the motor evaluation scale for upper extremity in stroke patients (MESUPES, part 1 to 4) on day 9 after admission to the hospital compared to baseline (Difference in scores on MESUPES between before treatment and day 9 after treatment).

(iii) Improvement of stroke severity measured with the National Institute of Health Stroke Scale (NIHSS) on day 9 after admission to the hospital compared to baseline (Difference in scores on NIHSS between baseline before treatment and day 9 after treatment).

(iv) Improvement of the Barthel Index (BI) on day 9 after admission to the hospital compared to baseline (Difference in scores on BI between baseline before treatment and day 9 after treatment)

(v) Improvement of the modified Rankin Scale (mRS) on day 90 after stroke compared to baseline (Difference in scores on mRS between baseline before treatment and day 90). The 90 day mRS is assessed via telephone interview by a blinded assessor.

(vi) Improvement of the Barthel Index (BI) on day 90 after stroke compared to baseline (Difference in scores on BI between baseline before treatment and day 90). The 90 day BI is assessed via telephone interview by a blinded assessor.

(vii) Improvement of the neglect (measured with the Catherine Bergego Scale) before and after every single intervention on day 2, day 5 and day 9.

(viii) Improvement of arm motor function (measured with the MESUPES) before and after every single intervention on day 2, day 5 and day 9.

The timing for the primary endpoint was chosen at day nine, because this is the mean residence time of stroke patients in the acute clinic before discharge to a rehabilitation center.

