## 9. Timeframes for Visits Outcome Measures

- Randomisation: Maximum 72h after stroke onset
  - Test 1: on day 2 after admission to hospital (+/- 1 day)
  - Test 2: on day 5 after admission to hospital (+/- 1 day)
  - Test 3: on day 9 after admission to hospital (+/- 1 day)
  - Test 4: on day 90 after stroke onset (+/- 5 days)
- The trunc control test (TCT) will be assessed at day 2 after admission to hospital before the first treatment (baseline), at day 5 and day 9 after treatment.
  - The National Institutes of Health Stroke Scale (NIHSS) will be assessed at day 2 after admission to hospital before the first treatment (baseline) and at day 9 after treatment.
  - The Catherine Bergego Scale (CBS) and the Motor Evaluation Scale for Upper Extremity in Stroke Patients (MESUPES) will be assessed at day 2, day 5 and day 9 after admission before and after treatment.
  - The modified Rankin Scale (mRS) and the Barthel Index (BI) will be assessed at day 2 after admission to hospital before the first treatment (baseline), at day 9 after treatment and at day 90 after stroke onset via a phone interview.
  - Investigators will record the occurrence of any serious adverse event and other safety outcomes that occur during hospital admission up to day 90.

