**Table 2: trial schedule**

|                                    | Screening visit | Baseline visit | Follow up visits |              |              |               |
|------------------------------------|-----------------|----------------|------------------|--------------|--------------|---------------|
| Procedures                  | 1) Screening    | 2) Enrollement | 3) Test 1        | 4) Test 2    | 5) Test 3    | 6) Test 4     |
|                                    | day 1-3         | day 1-3        | day 2(+/-1)      | day 5 (+/-1) | day 9 (+/-1) | day 90 (+/-5) |
| Check inclusion/exclusion criteria | X               | X              |                  |              |              |               |
| Randomisation                      |                 | X              |                  |              |              |               |
| Informed consent                   |                 | X              |                  |              |              |               |
| Clinical examination               | X               | X              | X                | X            | X            |               |
| Medical history                    | X               |                |                  |              |              |               |
| Demographic data                   | X               |                |                  |              |              |               |
| Concomitant medication             |                 | X              |                  |              | X            | X             |
| Adverse events                     |                 | X              | X                | X            | X            | X             |
| Imaging (CCT/MRI)                  | X               |                |                  |              |              |               |
| NIHSS                              | X               |                | X                |              | X            |               |
| mRS                                | Premorbid-mRS   |                | X                |              | X            | X             |
| CBS (5+6) (neglect test)           |                 |                | X                | X            | X            |               |
| MESUPES arm (1-4)                  |                 |                | X                | X            | X            |               |

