**(v) Modified Rankin Scale (mRS)  :**

The modified Rankin Scale is a single-item global outcomes rating scale that categorises level of functional independence with reference to pre-stroke activities and is an ordinal scale ranging from 0 (*no symptoms*), 1 (*no significant disability despite symptoms; able to carry out all usual duties and activities*), 2 (*slight disability: unable to carry out all previous activities but able to look after own affairs without assistance*), 3 (*moderate disability: requiring some help, but able to walk without assistance*), 4 (*moderately severe disability: unable to walk without assistance, and unable to attend to own bodily needs without assistance*), to 5 (*severe disability: bedridden, incontinent, and requiring constant nursing care and attention*), with a score of 6 allocated to those who die. Assessment is carried out by asking the patient about their activities of daily living, including outdoor activities.

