### 11.2 Statistical analysis plan

We plan an intention to treat analysis. For the primary endpoint (difference of scores in trunc control test between day 9 and baseline) an increase of 12 points (=12%) on the scale of the TCT was predefined as a meaningful difference pragmatically, due to lack of data in the literature, because an improvement of 12 points in the TCT indicates a clinical relevant improvement of self-dependence (i.e. no more need of an auxiliary person, no more need for an adjuvant as edge of bed for moving). Normal distribution of the variables will be tested by the Shapiro-Wilk-test. For the primary endpoint we assume non-Gaussian distribution and we plan an analysis of variance with the non-parametric Mann–Whitney-U-test. The primary endpoint (difference of scores in trunc control test between day 9 and baseline) will be tested concerning the influencing factors a priori known to potentially affect outcome (age, sex, NIHSS > or <10 at baseline; stroke site, thrombolysis and thrombectomy) to test whether they affected the treatment. Complications occurring between baseline and day 9 will be analyzed with the exact Fisher Test. An interim analysis is not planned. We have not defined any discontinuation criteria. Statistical analysis will be made by the principal investigator with support of a statistical institute.

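### Premorbid mRS is recorded before randomisation but not used in the day-90 mRS and Barthel comparisons, which leaves some precision unused in the trial's only masked outcomes (minor).

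*Protocol*

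**What the plan says.** - **Entry and timing.** Protocol section 5.1 allows a premorbid mRS of up to 3 and requires severe hemiparesis (MRC 2 or less). Table 2 lists "Premorbid-mRS" in the screening column, and randomisation stands in the later enrolment column.
- **Outcomes.** Section 8.2 (v) defines the day-90 mRS outcome as "Difference in scores on mRS between baseline before treatment and day 90". Section 8.2 (vi) defines the BI outcome as "Difference in scores on BI between baseline before treatment and day 90". Section 9 sets the baseline for both at day 2 after admission, before the first treatment.
- **Scale.** Section 10.1 (v) says that the mRS "categorises level of functional independence with reference to pre-stroke activities". Grade 4 is inability to walk or attend to bodily needs unaided, and grade 5 is bedridden.
- **Factor list.** Section 11.2 names "age, sex, NIHSS > or <10 at baseline; stroke site, thrombolysis and thrombectomy" and applies the list to the primary endpoint, the change in TCT. Premorbid mRS is not in it. No test or covariate is stated for the day-90 outcomes.
- **Masking and size.** Section 7 masks the assessor only for day-90 BI and mRS. Section 11.1 sets 20 patients per arm. Section 6 forgoes stratification for stroke severity because the trial is small.

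**The concern.** Pre-stroke disability plausibly affects where a patient stands at day 90. The protocol measures it at a point where knowledge of the arm cannot influence it, and then makes no further use of it. Its choice of baseline does not fill the gap. A day-2 score that is 4 or 5 for most patients hardly distinguishes someone who was fully independent before the stroke from someone who already needed help.

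If recovery stops at the pre-stroke level, a day-2 score of 4 or 5 leaves room for 4 or 5 grades of gain from premorbid 0, but only 1 or 2 from premorbid 3. Two arms of 20, unstratified, can differ noticeably on such a factor by chance. The outcomes affected are the only ones scored by someone unaware of the arm, so their precision is worth protecting.

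**Working it through.** The protocol has no calculation to reproduce here. It gives 20 per arm on feasibility grounds, with no alpha, power, SD or effect size for day 90. Every input below other than 20 per arm is an assumption, shown as a range.

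**1. How large a chance imbalance is plausible?** The standard error of the between-arm difference in mean premorbid mRS is SD × √(1/20 + 1/20).

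| Assumed SD | SE | 95% chance range | P(difference of 0.5 or more, either way) |
|---|---|---|---|
| 0.7 | 0.22 | ±0.43 | 2% |
| 0.9 | 0.28 | ±0.56 | 8% |
| 1.1 | 0.35 | ±0.68 | 15% |

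Counted as patients: if 15% to 40% have premorbid mRS 2–3, two independent Binomial(20, p) counts differ by at least 4 with probability 12% (p = 0.15) to 26% (p = 0.40), in either direction.

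**2. How much of that reaches day 90?** The shift is the imbalance times the slope of day-90 mRS on premorbid mRS. For slopes of 0.3 to 1.0, the 95% limits above give 0.43 × 0.3 = 0.13 up to 0.68 × 1.0 = 0.68 mRS points. The effect is one-to-one only at a slope of 1.

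**3. Does the unadjusted test break?** A null simulation used 20 per arm and 6,000 runs in each of six scenarios.

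- Premorbid grades 0–3 were distributed 60/20/12/8% or 40/25/20/15%.
- Day-2 mRS was 4 or 5 with equal chance.
- The latent day-90 score had mean 2.4, residual SD 1.1 and premorbid slope 0.3, 0.5 or 0.8. The day-90 grade could not be better than the premorbid grade.
- Mann–Whitney was applied to the mRS change.

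Overall type I error was 4.2% to 5.5%, which is nominal. Among the 11% to 17% of trials with an imbalance of at least 0.5 grade, false positives were about 10% to 15%. In the remaining trials they were about 2% to 5%.

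**4. What does adjustment gain?** In a linear model, residual variance falls by r², so 40 patients act like 40/(1 − r²).

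| Assumed r with mRS change | Variance removed | 40 patients act like |
|---|---|---|
| 0.2 | 4% | 42 |
| 0.3 | 9% | 44 |
| 0.4 | 16% | 48 |
| 0.5 | 25% | 53 |

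Splitting the score into 0–1 versus 2–3 loses part of this. For an underlying normal scale, the share of r² kept is φ(z)²/[p(1 − p)], where φ is the standard normal density and z its upper-p point. This is 0.43 at p = 0.15 and 0.62 at p = 0.40. For r = 0.3 to 0.5 the variance removed then runs from 0.43 × 9% ≈ 4% to 0.62 × 25% ≈ 16%, worth about 2 to 7 patients.

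**5. What if premorbid level only caps recovery?** Setting the slope to zero in the step 3 model and keeping only the cap, with latent day-90 means of 2.4, 3.0 and 3.5, the full score explained 0.2% to 5.6% of the variance in mRS change. By 40/(1 − 0.056), that is at most about 42 patients in place of 40. The gain is smallest where few patients recover far enough to meet the cap.

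The r² figures come from a linear model and are only a guide for ordinal or rank methods. None of these figures was derived for BI.

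**The case against.** The strongest objection is scope. Covariates for secondary outcomes are commonly left to a separate analysis plan, which is not at hand, and this protocol states no analysis at all for day 90. A reader might infer from the section 11.2 list that premorbid mRS has been ruled out. The documents do not support that: the list concerns TCT only and does not show how day 90 will be analysed. This stands. What remains is that the day-90 outcomes, as written, rest on the day-2 score alone.

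A reader might also infer that a difference in pre-stroke disability carries straight into the treatment comparison as bias. It does not. Allocation is random, so any imbalance is due to chance and the test's error rate already allows for it (step 3). The same is true of any unadjusted prognostic factor in a trial of 40.

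Third, the mechanism is inferred. The protocol does not say that premorbid mRS limits recovery, nor that day-2 scores are nearly all 4 or 5. Its wording of grades 1 and 2 already refers to the patient's usual or previous activities, which builds in part of the pre-stroke level. This also stands, and it is why the gain is given as a range reaching down to almost nothing.

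**Conclusion.** The point holds as a minor one. A pre-randomisation score of plausible prognostic value is collected, and the day-90 mRS and BI outcomes do not use it. The day-2 baseline they use instead probably corrects for little of the pre-stroke difference. The randomised comparison remains valid. The cost is unused precision and, in a minority of possible trials, an estimate distorted by chance imbalance.

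For mRS, the full score would remove about 4% to 25% of variance if r lies between 0.2 and 0.5. The gain is smaller with a two-way split and near zero if premorbid level acts only as a cap. The size rests wholly on assumed correlations and premorbid distributions, and it is not established for BI. Because these are two of eight secondary outcomes in a declared pilot, the change is optional.

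**What to change.** State in section 11.2 that the between-arm comparisons of day-90 mRS and day-90 BI are adjusted for the premorbid mRS taken at screening.

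- **Preferred:** one ordered term (0–3) in a proportional-odds model or a rank-based ANCOVA. This keeps the information that a split would lose.
- **Alternative:** a van Elteren test stratified 0–1 versus 2–3. At 15% prevalence the upper stratum would hold only about 6 of the 40 patients (0.15 × 40).
- **In either case:** report premorbid mRS by arm.

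Adding premorbid mRS to the existing factor list in section 11.2 would not serve this purpose, since that list applies only to TCT.

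The cost is one sentence and one model term, with no new data. Fixing the term in advance also avoids choosing covariates after an imbalance has been seen.

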### **8.3 Safety Outcomes**

All adverse events and serious adverse events are recorded and assessed by the investigators throughout the trial until day 90 according to standard definitions. All deaths until 3 months and the serious adverse during the hospital stay will be evaluated and forwarded to a medical expert for assessment of relatedness to the study treatment.

## 9. Timeframes for Visits Outcome Measures

- Randomisation: Maximum 72h after stroke onset
  - Test 1: on day 2 after admission to hospital (+/- 1 day)
  - Test 2: on day 5 after admission to hospital (+/- 1 day)
  - Test 3: on day 9 after admission to hospital (+/- 1 day)
  - Test 4: on day 90 after stroke onset (+/- 5 days)
- The trunc control test (TCT) will be assessed at day 2 after admission to hospital before the first treatment (baseline), at day 5 and day 9 after treatment.
  - The National Institutes of Health Stroke Scale (NIHSS) will be assessed at day 2 after admission to hospital before the first treatment (baseline) and at day 9 after treatment.
  - The Catherine Bergego Scale (CBS) and the Motor Evaluation Scale for Upper Extremity in Stroke Patients (MESUPES) will be assessed at day 2, day 5 and day 9 after admission before and after treatment.
  - The modified Rankin Scale (mRS) and the Barthel Index (BI) will be assessed at day 2 after admission to hospital before the first treatment (baseline), at day 9 after treatment and at day 90 after stroke onset via a phone interview.
  - Investigators will record the occurrence of any serious adverse event and other safety outcomes that occur during hospital admission up to day 90.

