## 6. Screening and Randomisation:

All potentially eligible patients are screened on the first day after admission to the stroke unit and during the first 72h after stroke onset, in case of deterioration after admission. Eligible patient with written informed consent will be enrolled and randomly assigned (1:1) to receive usual stroke unit care with conventional physiotherapy (control group) or Vojta therapy (interventional group).

| Arm                  | Therapy                    |
|----------------------|----------------------------|
| interventional group | Vojta therapy              |
| control group        | conventional physiotherapy |

Randomisation will be performed with sealed, opaque and sequentially numbered envelope. The investigators are instructed to assign the patient according to the envelope with the lowest randomisation number. Randomisation has to be done within 72 hours after onset of symptoms or after patients were last seen well and can be done by a physiotherapist or the investigator, who enrolles the subject. Stratification for stroke severity was disclaimed due to the small sample size.

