## 7. Masking:

Masking of treatment is not possible because of the different appearance of the two physiotherapeutic approaches. Blinded assessment meanwhile hospital stay is not feasible, because it cannot be ensured that assessments are conducted by an evaluator physical therapist different from the treating physical therapist, due to logistic reasons. The trial is observer blinded only for the secondary clinical outcome Barthel Index and modified Ranking Scale at day 90. All other outcome assessors will have knowledge of the interventions assigned to individual participants.

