## **8. Predefined Outcome Measures**

### **8.1. Primary Outcome Measure:**

Improvement of postural control measured with the trunc control test (TCT) on day 9 after admission to the hospital compared to baseline (Difference in scores on TCT scale between baseline and day 9)

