| Trunc Control Test (TCT)           |                 |                | X                | X            | X            |               |
| Barthel Index                      |                 |                | X                |              | X            | X             |

CCT=cranial computed tomography. MRI=magnetic resonance imaging. CBS=Catherine Bergego scale (item 5 and 6) (=Neglect Test). MESUPES= motor evaluation scale for upper extremity in stroke patients (item 1 to 4 = MESUPES arm).

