## **12. Therapeutical intervention and staff qualification**

### 12.1 General comments concerning intervention and treatment time:

General management on the stroke unit of all included patients follows the standards of treatment defined in the contemporary European  (European Stroke Initiative [EUSI] and European Stroke Organization [ESO]) and national guidelines.

Patients will be either randomised to Vojta therapy or conventional physiotherapy within 72 hours after stroke onset. For ethical reasons, all patients received standard physiotherapy until randomisation in case randomisation is delayed e.g. by diagnostic procedures within and up to 72 hours. Eligible patients are preferred to get their MRI or CT scan as soon as possible in order to confirm their stroke (see „Imaging“).

Treatment sessions consist of 40 minutes once daily for 7 days for all patients, including treatment, mobilization and testing on weekend if necessary. Before testing on day 9 (+/-1 day) therefore all patients will have 7 treatment sessions. Assessments will be performed by two physiotherapist (one from the Vojta- one from the control group) following the four-eyes principle. In case of disagreement in scoring, a third physiotherapist should conduct an additional assessment.

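### As scheduled, the baseline TCT comes after randomisation and its raters know the arm, so avoidable rater bias can enter the primary change score

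*Protocol*

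**What the plan says.** Section 8.1 defines the primary outcome as "Difference in scores on TCT scale between baseline and day 9". Section 9 sets the time of the first score: "The trunc control test (TCT) will be assessed at day 2 after admission to hospital before the first treatment (baseline". It names the first treatment as the limit and does not mention randomisation.

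Table 2 numbers the visits in the order "2) Enrollement | 3) Test 1". Consent and randomisation are marked at Enrolment, which stands under the baseline-visit heading. Test 1 is the first column under "Follow up visits". The row "Trunc Control Test (TCT" is empty at Screening and Enrolment and marked at Tests 1, 2 and 3.

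On masking, section 7 limits observer blinding to the Barthel Index (BI) and the modified Rankin Scale (mRS) at day 90 and adds: "All other outcome assessors will have knowledge of the interventions assigned to individual participants". Section 6 says that randomisation "can be done by a physiotherapist or the investigator, who enrolles the subject". Section 12.1 says: "Assessments will be performed by two physiotherapist (one from the Vojta- one from the control group) following the four-eyes principle". A third physiotherapist assesses the patient if the two disagree.

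**The concern.** A baseline score should not depend on the allocation. The simplest guarantee is to record it before anyone can know the arm. Here the visit order runs the other way and no sentence corrects it.

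The baseline enters the primary endpoint with full weight. A harsher grade at baseline in one arm counts as extra improvement in that arm, even if day 9 is scored perfectly. Section 2 records that the team has already seen posture improve with Vojta therapy, so rater expectation is a realistic worry.

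The trial's only blinded outcomes are affected too. Section 8.2 (v) and (vi) analyse day-90 mRS and BI as change from baseline, and section 9 takes that baseline from the same open Test 1. The blinding therefore covers only the follow-up half of those differences.

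**Working it through.** The protocol gives no figure to reproduce: section 11.1 says a sample size calculation was not feasible, and no SD, alpha or power is stated. The check is a reading of the schedule, followed by arithmetic on the TCT grades.

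**Order of events**
- Randomisation: visit 2, day 1-3 (Table 2).
- First TCT: visit 3, day 2 (+/-1), that is day 1 to 3 (section 9, Table 2).
- The two spans cover the same day numbers, so scoring before randomisation is possible. Nothing requires it, and the visit numbering puts randomisation first.

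**Does the stated reason cover baseline?** Section 7 explains open in-hospital assessment by the assessor possibly being the treating therapist. Before the envelope is opened, that therapist cannot know the arm either. The reason therefore holds for days 5 and 9 but not for a baseline scored before allocation.

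**Weight of a baseline error.** Change = (day-9 score) − (baseline score). If the baseline is recorded e points too low, the change is e points too large.

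**Size in points.** Section 10.1 grades each item 0, 12 or 25. One step is 12 − 0 = 12 or 25 − 12 = 13 points. For one patient, that is at least the whole 12-point meaningful difference in section 11.2. If a fraction f of one arm is graded one step low on one item, the mean difference shifts by at most 12f to 13f:
- f = 0.25: 3.0 to 3.25 points
- f = 0.5: 6.0 to 6.5 points
- f = 1: 12 to 13 points

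An item already at 0 cannot be graded lower, so the real shift would be smaller.

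**Effect on the test, normal approximation.** Take 20 per arm (section 11.1), no true effect and an assumed two-sided alpha of 0.05. The chance of a significant result for the favoured arm is Φ(12f / (SD × √(2/20)) − 1.96), nominally 2.5%. With f = 0.5 and an assumed SD of change of 15, it is Φ(6/4.74 − 1.96) = 24.4%. With SD 20, 25 and 30 it is 15.6%, 11.5% and 9.2%. With f = 0.25 the four figures are 9.2%, 6.9%, 5.7% and 5.0%.

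**Effect on the test, simulation.** The planned Mann-Whitney test was applied to simulated four-item TCT scores, with 20 per arm, no true effect and 3,000 trials per setting. Mean baseline TCT was set at about 25 or 46, and the SD of change was about 16 or 14. These settings are assumptions.

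| f | Mean shift, baseline 25 / 46 | Two-sided rejection, baseline 25 / 46 |
|---|---|---|
| 0 | 0.1 / −0.1 | 4.4% / 4.9% |
| 0.25 | 1.7 / 2.6 | 5.3% / 6.7% |
| 0.5 | 3.4 / 5.0 | 8.5% / 16.0% |
| 1 | 6.6 / 10.2 | 18.1% / 48.8% |

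The shifts lie below 12f, as the floor implies. At f = 0.25 the inflation is slight. It becomes clear only when half the arm or more is misgraded in the same direction.

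**The case against.** The strongest reply is that the protocol already limits this risk and is open about it. Two raters, one from each team, score every assessment, and a third resolves disagreement. A harsh Vojta baseline would need the control-team rater to agree, or the third rater to side with it. The TCT grades have behavioural anchors (section 10.1). Section 7 discloses the open assessment, and section 11.1 calls this a pilot.

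This lowers the likely size of any bias, and the figures above take no account of it. It does not remove the risk: both raters know the arm, and section 7 makes no exception for the third. Disclosure does not justify an unmasked baseline when the reason given does not reach it.

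Two further objections stand:
- The order is inferred from the numbering in Table 2. No sentence states it, and the windows overlap.
- The planned primary test has no baseline-TCT covariate, so there is no TCT adjustment to undermine. The baseline score among the influencing factors in section 11.2 is NIHSS above or below 10. Table 2 also schedules an NIHSS at Screening, although section 9 takes the baseline NIHSS from Test 1.

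A reader might also infer that section 7 contradicts sections 12.1 and 12.3. It does not. With one rater from each team, one of the pair always comes from the patient's own treatment team and may be the treating therapist, which is what section 7 says cannot be excluded.

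**Conclusion.** The point holds as a design weakness that can be avoided. The plan permits, and by its visit order implies, that the baseline TCT and the other pre-treatment Test 1 scores are taken with the allocation known. Allocation-dependent rater bias can then enter the primary change score and the day-90 mRS and BI changes.

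The size is bounded but not known: at most about 12f to 13f points for one step on one item in a fraction f of one arm. The value of f, the SDs and the simulated score distributions are assumptions, and the documents give neither the direction nor the extent of any bias.

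A reader might infer that the protocol expressly places baseline after randomisation, or that a shift of 3 or 6 points is to be expected. The documents support neither. The first is an inference from Table 2, and the second rests on assumed fractions without credit for the floor or the paired scoring.

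**What to change.** In sections 6 and 9 and in Table 2, move the pre-treatment Test 1 scores (TCT, NIHSS, CBS, MESUPES, mRS, BI) to the Enrolment visit, after consent. Require them to be recorded, signed and timed before the randomisation envelope is opened. The post-therapy CBS and MESUPES scores of Test 1 stay after treatment. State in section 7 that these baseline scores are taken before the allocation is known.

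This needs no additional test, and the existing pair of raters can do the scoring. It removes allocation-dependent bias from the baseline.

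The cost is tighter sequencing. Randomisation must fall within 72 hours of onset, while Test 1 is timed from admission, so patients admitted late have less time for the battery. A few patients may be scored and then not randomised.

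The change does not mask day 9, the other half of the primary difference. That should still be reported as a limitation.
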